## 5.14 - Criteria for discontinuation of treatment

- DLT as defined by grade 3 or 4 toxicity according to the National Cancer Institute Common Terminology Criteria for Adverse Events, version 4.0.
- Grade 2 intracranial hemorrhage
- Request by the patient for discontinuation.

# 6 - Regulatory and Reporting Requirements

## 6.1 - Adverse Events (AE)

### 6.1.1 - Adverse Event Definition

An adverse event is an untoward medical event in a patient which does not necessarily need to have a casual relationship with the treatment. AEs will be reported according to the NCI Common Terminology Criteria for Adverse events (CTCAE) and Common Toxicity Criteria (CTC) version 4.0.

### 6.1.2 - Attribution of an AE

The relationship of an AE to the study medication will be established:

- Definite – AE Clearly related to the study treatment
- Probable – AE likely related to the study treatment
- Possible – AE may be related to the study treatment
- Unlikely – AE doubtfully related to the study treatment
- Unrelated – AE clearly not related to study treatment

## 6.2 - Serious Adverse Event Reporting (SAE)

An SAE is an adverse event that is:

- Life threatening
- An important medical event in the opinion of the principal investigator
- Results in:
  - Death
  - In-patient hospitalization or prolonged existing hospitalization
  - Persistent or significant disability or incapacity
  - Congenital anomaly/birth defect
  - Or in the opinion of the investigator represents significant hazard or potentially serious harm to subjects or others

### 6.2.1 - Non-serious adverse event definition

An adverse event is any untoward medical occurrence that does not meet the definition of serious (section 6.2). These do not have to be reported via expedited reported mechanism unless the treating physician feels it necessary. All AEs (including SAEs) must be reported in routine case report forms.

## 6.3 - Unexpected Adverse Event

An unexpected adverse event is any event where the nature and the severity of the event is not consistent with the previously reported documentation including the Investigator’s Brochure.

## 6.4 - AE Reporting

Adverse events which are unexpected and attributed to the investigational product must be reported to the Internal Review Board and Data Safety Monitoring Committee. All SAEs and AEs that require withdrawal of a patient from the study should be reported immediately and no later than 48 hours from the time study personnel learn of the event. All other events should be reported within 10 days of the study personnel learning of the event.

### 6.4.1 - Follow-up of AEs

AEs must be followed until the have resolved or have become stable with no resolution expected. Follow up of AEs must be recorded in medical record and on the case report forms.

## 6.5 - Expected AEs that do not require expedited reporting

There are numerous complications that could result form the surgical procedure itself. If any of these occurred, they will be assessed by the PI and provided the appropriate grade and attribution. Reporting will follow the guidelines detailed above.

## 6.6 - Investigator Reporting to the FDA

Serious adverse events (SAEs) that are unlisted/unexpected, and at least possibly associated to the drug, and that have not previously been reported in the Investigators brochure, or reference safety information document should be reported promptly to the Food and Drug Administration (FDA) by telephone or by fax. Fatal or life threatening SAEs that meet the criteria for reporting to the FDA must be reported to the FDA within 7 calendar days after awareness of the event. All other SAEs that meet the criteria for reporting to the FDA must be reported to the FDA within 15 calendar days after awareness of the event. A clear description of the suspected reaction should be provided along with an assessment as to whether the event is drug or disease related.

## 6.7 - Data Saftey Monitoring Plan

The data and safety monitoring plan will involve the continuous evaluation of safety, data quality and data timeliness. Investigators will conduct continuous review of data and patient safety at their regular Disease Group meetings (at least monthly) and the discussion will be documented in the minutes. The PI of the trial will review toxicities and responses of the trial where applicable at these disease center meetings and determine if the risk/benefit ratio of the trial changes. Frequency and severity of adverse events will be reviewed by the PI and compared to what is known about the agent/device from other sources; including published literature, scientific meetings and discussions with the sponsors, to determine if the trial should be terminated before completion. Serious adverse events and responses will also be reviewed by the OSUCCC Data and Safety Monitoring Committee (DSMC). The PI will also submit a quarterly progress that will be reviewed by the committee per the DSMC plan. All reportable Serious Adverse Events (SAE) will also be reported to the IRB of record as per the policies of the IRB.

|  | Within 4 weeks prior to catheter Placement | Day of surgery, catheter placement, and infusion | Day after surgery | Post-infusion day 1 | Day 7 | Day 14 | Day 28 | Week 8 | Week 12 | Week 16 | Week 22 | Week 30 |
| --- | --- | --- | --- | --- | --- | --- | --- | --- | --- | --- | --- | --- |
| Informed Consent | X |  |  |  |  |  |  |  |  |  |  |  |
| Inclusion/Exclusion  Criteria | X |  |  |  |  |  |  |  |  |  |  |  |
| Pathology | X | X |  |  |  |  |  |  |  |  |  |  |
| Medical History | X |  |  | X |  |  | X | X | X | X | X | X |
| Concomitant Meds | X | X |  | X |  |  | X | X | X | X | X | X |
| Physical Exam and Vital Signs | X | X | X | X |  | X | X | X | X | X | X | X |
| Neurological examination | X | X | X | X |  | X | X | X | X | X | X | X |
| MMSE | X | X | X | X |  | X | X | X | X | X | X | X |
| Performance Status Determination | X | X | X | X |  | X | X | X | X | X | X | X |
| CBC with differential and platelets, | X | X | X | X | X | X | X | X | X | X |  |  |
| Comprehensive Metabolic Profile | X | X | X | X | X | X | X | X | X | X |  |  |
| Pregnancy Testing | X |  |  |  |  |  |  |  |  |  |  |  |
| MRI Brain^1^ | X |  |  |  |  |  |  | X |  | X |  | X |
| AE monitoring | X | X | X | X | X | X | X | X | X | X | X | X |
| CT Brain |  | X |  |  |  |  |  |  |  |  |  |  |

7 – Study Calendar

1. MRI will be performed after catheter removal.

# 8 - Clinical Response and Endpoint Definitions

## 8.1 - Primary endpoint

The primary endpoint is to establish the dose-limiting toxicity and maximum tolerated dosage of convection enhanced delivery of carboplatin. DLT is defined as grade 3 or 4 toxicity as defined by the National Cancer Institute – Clinical Trials Group version 4.0 that is attributable to the study drug or protocol. In addition, grade 2 intracranial hemorrhage is a DLT. The maximum tolerated dosage is defined as the dose level below that causing DLT in at least two patients.

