# 5 - Treatment Plan

5.1 - Study Design:

Phase I dose escalation study

5.2 - Proposed trial:

Carboplatin in a volume of 54 ml will be administered intracerebrally by convection enhanced delivery at a flow rate of 0.75 ml/hr over 72 hr. The first patient will receive an initial starting dose of 2 µg over 72 hrs (0.667 µg/24 hr). This first patient will be observed for 28 days after completion of the infusion, prior to enrollment of additional patients. In the absence of dose-limiting toxicity (DLT), 3 more patients will be entered at the next higher dose level, which will be double the prior dose (i.e., 4 µg over 72 hrs). If 1of 3 patients exhibits DLT, an additional 3 patients will be entered at that dose level. Dose escalation will continue until DLT occurs in at least 2 out of 6 patients. The maximum tolerated does (MTD) will be defined as the highest dose level at which 3/3 or 5/6 patients could be treated without DLT. Dosage escalation will proceed in subsequent cohorts of 8 µg, 16 µg, 32 µg, 64 µg, 85 µg, 107 µg and 128 µg. If the MTD has not been reached, we will submit a request to the FDA with a schedule for continued escalation until DLT is reached. If 2 of 3 patients demonstrate DLT at 2 µg, the dose will be reduced to 1 µg for the next three patients. DLTs are defined, in the presence of supportive care, as any Grade 3 or 4 toxicity that is possibly, probably, or definitely related to the study drug. The maximum tolerated dosage is defined as the dose level below that causing DLT in at least two patients. The length of the DLT window will be at least 28 days, and this time interval must elapse before completion of one cohort and initiation of the next.

5.3 - Population:

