## 5.13 - Dose-Limiting Toxicity (DLT)

DLTs are defined, in the presence of supportive care, as any Grade 3 or 4 toxicity that is possibly, probably, or definitely related to the study drug. The maximum tolerated dosage is defined as the dose level below that causing DLT in at least two patients. The length of the DLT window will be at least 28 days, and this time interval must elapse before completion of one cohort and initiation of the next.

Non-hematologic toxicities such as rash, nausea, vomiting and hypertension will only be considered DLTs if they remain grade 3 or greater despite maximal medical therapy 72 hours after maximal medical therapy is initiated. The first deep venous thrombosis or pulmonary embolism will not be considered a DLT because these complications are common among patients with high-grade gliomas. Patients who develop DVT and/or PE may receive anticoagulation therapy and resume the clinical trial once clinically stable. A second DVT or PE on optimal medical therapy will be considered a DLT.

| **Number of Patients with DLT**  **At a Given Dose Level** | **Escalation Decision Rule** |
| --- | --- |
| 0 out of 3 | Enter 3 patients at the next dose level |
| > 2 | Dose escalation will be stopped. This dose level will be declared the maximally administered dose (highest dose administered). Three (3) additional patients will be entered at the next lowest dose level if only 3 patients were treated previously at that dose. |
| 1 out of 3 | Enter at least 3 more patients at this dose level.   - If 0 of these 3 patients experience DLT, proceed to the next dose level. - If 1 or more of this group suffer DLT, then dose escalation is stopped, and this dose is declared the maximally administered dose. Three (3) additional patients will be entered at the next lowest dose level if only 3 patients were treated previously at that dose. |
| <1 out of 6 at highest dose level below the maximally administered dose | This is generally the recommended phase 2 dose. At least 6 patients must be entered at the recommended phase 2 dose. |

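### The DLT definition behind the primary endpoint differs between sections 5.2/5.13 and 8.1, so the same events can lead to different escalation decisions and a different MTD

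*Protocol*

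**What the plan says.** Four places in the protocol describe a DLT.

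- **Section 5.2 (Proposed trial):** "any Grade 3 or 4 toxicity that is possibly, probably, or definitely related to the study drug". There is no haemorrhage clause and no exemption.
- **Section 5.13 (Dose-Limiting Toxicity), beside the escalation table:** the same core sentence, defining DLTs "as any Grade 3 or 4 toxicity that is possibly, probably, or definitely related to the study drug". Two exemptions follow that appear nowhere else. Non-haematologic toxicities, with four examples, "will only be considered DLTs if they remain grade 3 or greater despite maximal medical therapy 72 hours after maximal medical therapy is initiated". Also, "The first deep venous thrombosis or pulmonary embolism will not be considered a DLT".
- **Section 8.1 (Primary endpoint):** grade 3 or 4 toxicity "that is attributable to the study drug or protocol. In addition, grade 2 intracranial hemorrhage is a DLT". No exemptions are given.
- **Section 5.14 (Criteria for discontinuation of treatment):** the first bullet reads "DLT as defined by grade 3 or 4 toxicity according to the National Cancer Institute Common Terminology Criteria for Adverse Events, version 4.0", with no attribution condition. A separate bullet lists "Grade 2 intracranial hemorrhage".

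Sections 5.12 and 5.13 turn the DLT count into decisions: 0 of 3 escalates, 1 of 3 adds three patients, and two DLTs stop escalation, with the next lower level taken as the MTD. Section 8.1 defines the MTD from the same count. No section gives one definition precedence.

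**The concern.** The primary endpoint is a dose level reached by counting DLTs. If the count depends on which section the investigator opens, the endpoint is not uniquely determined by the written rules. Clinicians also apply the definition cohort by cohort during the trial, so an analysis document written later cannot undo an escalation already made.

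The two main differences concern foreseeable events. Every patient has two to four catheters placed in the brain (section 5.6), and a CT after surgery looks for intracranial haemorrhage (section 5.10). Section 6.5 anticipates complications of the surgical procedure. Whether such events count decides whether the MTD describes the drug alone or the drug together with its delivery.

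**Working it through.** The plan states no figure on this point, so there is none to reproduce. The check has two parts.

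**1. Same events, two definitions (no rates assumed).** Take a cohort of three infused patients. The stop rule is the one in the paragraph below the table in 5.13: two DLTs stop escalation.

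| Events in the cohort | Count under 5.2/5.13 | Count under 8.1 |
|---|---|---|
| One grade 2 haemorrhage | 0/3, escalate | 1/3, add three patients |
| Two grade 2 haemorrhages | 0/3, escalate | 2/3, stop, MTD is the level below |
| Two grade 3 events due only to the catheter procedure | 0/3, escalate | 2/3, stop, MTD is the level below |
| One drug-related grade 3 event and one grade 2 haemorrhage in another patient | 1/3, add three patients | 2/3, stop, MTD is the level below |

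The haemorrhage rows do not depend on any causality judgement: a grade 2 event cannot meet a grade 3 or 4 definition. The catheter row assumes the events are judged not even possibly related to the drug.

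**2. Illustration of size.** The protocol gives no rate for such events, so b below is an assumption.

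Inputs:
- b is the per-patient probability of an event that counts only under 8.1, constant across dose levels.
- The drug causes no DLT.
- There are nine levels (Levels 1 to 9, section 5.12.1), each with the 3+3 rule. The accrual ceiling of 42 in section 9 is ignored.

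A level is passed with 0 of 3, or with 1 of 3 followed by 0 of 3:

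P(pass) = (1−b)³ + 3b(1−b)² × (1−b)³ = (1−b)³ + 3b(1−b)⁵

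P(stop before clearing nine levels) = 1 − P(pass)⁹

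| b | P(pass) | P(pass)⁹ | P(stop) under 8.1 |
|---|---|---|---|
| 1% | 0.9703 + 0.0285 = 0.9988 | 0.990 | about 1% |
| 2% | 0.9412 + 0.0542 = 0.9954 | 0.960 | about 4% |
| 5% | 0.8574 + 0.1161 = 0.9734 | 0.785 | about 22% |
| 10% | 0.7290 + 0.1771 = 0.9061 | 0.412 | about 59% |
| 20% | 0.5120 + 0.1966 = 0.7086 | 0.045 | about 95% |

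Section 5.2 may enter only one patient at the first level, whereas 5.12 enters three. Leaving that level out (eighth power) gives 19%, 55% and 94% for b = 5%, 10% and 20%, so this detail matters little.

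Under 5.13 the corresponding probability is lower. It is 0% only if no such event is ever judged possibly drug-related.

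**The case against.** Several arguments limit the point, and most of them stand in part.

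- **Procedural events may be rarer in the count than they look.** Resection is already recommended for every eligible patient (sections 4.1 and 4.2), so its complications are arguably not attributable to the protocol; those of the catheters and infusion are. Patients too unwell to be infused have the catheters removed (5.9), fall outside the endpoint analysis and are replaced (section 9). A reader might infer that craniotomy complications will enter the count at every level. The documents do not support that; they show only that qualifying events can occur at any level.
- **The two definitions are closer in practice than 0% against 22% to 95%.** Possible relation is a low threshold. Section 6.1.2 opens with relationship to the study medication but grades each category against study treatment, which section 9 describes as catheter placement plus carboplatin delivery. Some procedural events could therefore count under 5.13 as well. This stands, and it shows that the attribution scale carries the same ambiguity.
- **Counting delivery toxicity may be intended.** Section 8.1 concerns convection enhanced delivery of carboplatin, so a stop caused by the procedure is not necessarily a false MTD. This also stands: the defect is the disagreement between the versions.
- **Sections 5.14 and 5.2 are weaker conflicts.** 5.14 is a discontinuation list and does not drive escalation; its separate haemorrhage bullet is compatible with 8.1. The exemptions in 5.13 can be read as detail that 5.2 omits. Even so, the text does not say whether they apply to the endpoint in 8.1.
- **Neurotoxicity and death.** A reader might take the open list of examples in the 72-hour exemption to cover transient neurotoxicity. That is speculative, since the examples are rash, nausea, vomiting and hypertension, and section 5.10 sets apart the primate toxicity as following brainstem infusion. A reader might also infer that the trial would overlook a drug-related death. It would not: deaths are serious adverse events (6.2), with expedited FDA reporting where section 6.6 applies and safety committee review (6.7). But those routes do not put a death into the DLT count.

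None of this removes the conflict between 5.2/5.13 and 8.1 on attribution and on grade 2 haemorrhage.

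**Conclusion.** The point holds as an internal contradiction in the definition of the primary endpoint. For two kinds of event, grade 2 intracranial haemorrhage and grade 3 or 4 events due to the procedure rather than the drug, the written rules give different DLT counts. Two such events in a cohort of three separate escalation from stopping with a lower MTD. The haemorrhage case needs no assumption about rates or attribution.

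The MTD differs only if such events occur. How often that would change the result cannot be determined from the documents. Under the stated assumptions the chance of stopping early under 8.1 runs from about 1% at b = 1% to about 95% at b = 20%, and the gap from 5.13 is smaller than those figures to the extent that attribution is imperfect.

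Separately, every version stops at grade 4, although the 5.13 exemption refers to grade 3 or greater. Read literally, a drug-related death is not a DLT. This is a gap shared by all versions, not a conflict between them.

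**What to change.** Reconcile sections 5.2, 5.13, 5.14 and 8.1 into one DLT definition. State it once, replace the other versions with a cross-reference, and use it for both the escalation table and the primary endpoint. The reconciled text must settle four things:

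1. the scope of attribution (drug only, or drug and procedure), worded consistently with the scale in section 6.1.2;
2. whether grade 2 intracranial haemorrhage counts;
3. how grade 5 events are handled;
4. whether the exemptions in 5.13 apply to the primary endpoint.

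Which clinical rule applies in each case is for the sponsor's clinicians. The cost is a protocol wording amendment, with no extra patients.

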The table above describes the dose escalation algorithm. If a DLT is encountered in 1 patient at a given dose level/cohort, an additional 3 patients will be enrolled at that dose level. If 2 patients in any cohort experience a DLT than the next lower dose level will be considered the MTD and no further dosage escalation will be performed. Three additional patients will be treated at the next lowest dose level if only 3 patients were previously treated at that level. If 3 patients are treated at the maximum dose without experiencing a DLT, an additional 3 patients will be treated at that dose level. At least 6 patients must be treated at the MTD. At least 28 days must elapse between the completion of one cohort to the beginning of the next cohort.

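### Section 8.1 counts grade 2 intracranial haemorrhage as a DLT while the escalation sections 5.2 and 5.13 do not, so the same patients can lead to different escalation decisions

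*Protocol*

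**What the plan says.** Protocol section 8.1 makes DLT and MTD the primary endpoint. It defines a DLT as a grade 3 or 4 event "attributable to the study drug or protocol" and then adds: "In addition, grade 2 intracranial hemorrhage is a DLT". That sentence carries no attribution condition of its own.

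Sections 5.2 and 5.13 both define a DLT as "any Grade 3 or 4 toxicity that is possibly, probably, or definitely related to the study drug". Section 5.13 then qualifies this. Some non-haematologic toxicities count only if they persist despite treatment, and a first venous thrombosis or pulmonary embolism does not count. It says nothing about a grade 2 bleed. The same section holds the escalation table, and it fixes the time frame: "The length of the DLT window will be at least 28 days". Its stopping rule reads: "If 2 patients in any cohort experience a DLT than the next lower dose level will be considered the MTD".

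Section 5.14 gives the reasons for discontinuing treatment. One is "DLT as defined by grade 3 or 4 toxicity", and a separate one is "Grade 2 intracranial hemorrhage".

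**The concern.** The DLT count decides, cohort by cohort, whether the next patients receive a higher dose, and it fixes the MTD at the end. The definition therefore has to be settled in the protocol before any cohort is read; it cannot be left to an analysis plan. A team working from section 5 would not count a grade 2 intracranial bleed. An analyst working from section 8 would. Nothing says which section governs.

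The event is foreseeable here. Patients have a resection, two to four catheters placed in the brain, a 72-hour infusion and catheter removal at the bedside. The protocol names this grade of bleed in both 5.14 and 8.1. The difference in attribution scope causes the same trouble at grade 3 or 4: an event put down to the catheter and not to carboplatin is a DLT under 8.1 but not under 5.13.

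**Working it through.** There is no stated sample size, power or error rate that rests on the DLT definition, so there is no figure to reproduce. The check applies the protocol's own rules twice to the same patients.

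**Inputs**
- Escalation rules (5.13, table and the paragraph below it): no DLT in 3 means go up; 1 in 3 means add three patients; after that, no DLT in the added three means go up, and one or more means stop.
- Two patients with DLT means stop, with the next lower level taken as MTD. The table row for this case prints as more than 2 in the text at hand. The paragraph below the table and the MTD definition both use two patients, so two or more is used here.
- A cohort of three, as in 5.12. Section 5.2 describes a single first patient at the starting dose.
- The protocol gives no bleed rate, and none is assumed.

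**Notation.** Let *b* be the number of patients whose only relevant event is a grade 2 intracranial bleed within the DLT window, and *d* the number with a DLT under both definitions. The count is *d* under 5.13 and *b* + *d* under 8.1. It is unclear whether the added sentence in 8.1 inherits the attribution condition before it. The bleeds below are taken to be attributable, so they count under 8.1 on either reading. Under 5.13 they fail on grade alone.

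**First three patients**

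| b | d | Count, 5.13 | Decision, 5.13 | Count, 8.1 | Decision, 8.1 |
|---|---|---|---|---|---|
| 1 | 0 | 0/3 | escalate | 1/3 | add 3 |
| 2 | 0 | 0/3 | escalate | 2/3 | stop |
| 1 | 1 | 1/3 | add 3 | 2/3 | stop |
| 1 | 2 | 2/3 | stop | 3/3 | stop |

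**After expansion.** Suppose the first three patients include one DLT under both definitions, and the only event in the next three is a grade 2 bleed. The count is 1/6 under 5.13, so escalate. It is 2/6 under 8.1, so stop, and the next lower level is the MTD.

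**When the paths rejoin.** Take one bleed and no other DLT in the first three, then no event in the added three. Under 8.1 the count is 1/6 and escalation proceeds, as it would have done under 5.13. The difference is three more patients at that level and their observation time.

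**Attribution.** Replace the grade 2 bleed by a grade 3 event judged to be caused by the catheter procedure and not by the drug. It adds 0 to the count under 5.13 and 1 under 8.1, so the same table applies.

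**The case against.** The strongest reply is that the sections are cumulative. The sentence in 8.1 is worded as an addition and stands in the chapter on endpoint definitions; 5.14 names the same bleed as a reason to stop treatment. On that reading 5.2 and 5.13 are incomplete and there is no rival rule. This reading is possible, but it does not remove the conflict. Section 5.13 carries the title of the DLT definition and reads as complete, with its own exceptions. Section 8.1 does not simply add to it: it restates the definition with a wider attribution scope and without those exceptions. Section 5.14 sets the bleed beside DLT, not inside it.

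Three stronger readings are tempting, and the protocol does not support them.
- A reader might infer that any such bleed changes the MTD. It changes only if the count crosses from 0 to 1 or from 1 to 2, and even then the paths can rejoin, as shown. With two other DLTs both definitions stop.
- A reader might measure the harm as the gap between the next dose up under 5.13 and the next dose down under 8.1. That compares a dose still to be tested with a candidate MTD. Under 5.13 the MTD is not yet known at that point, and under 8.1 three more patients are treated at the lower level if only three were treated there before.
- A reader might infer that a surgical bleed present before infusion would be counted against the drug. Section 5.14 makes a grade 2 bleed a reason to discontinue, with no timing limit. Section 5.9 removes the catheters if the patient's condition rules out infusion, and section 9 replaces patients who did not receive study treatment. That case is largely covered.

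**Conclusion.** The inconsistency is real and sits in the rule behind the primary endpoint. Its size is best stated as changed decisions: escalate against add three for one grade 2 bleed in three patients; escalate against stop for two; add three against stop for one bleed beside one other DLT. The declared MTD can differ as a result, but this is not certain. These results rest on the protocol's rules alone, with cohorts of three, two or more DLTs as the stopping point, and bleeds that occur within the DLT window and are attributable. How often this would happen cannot be stated, because the protocol gives no bleed rate. The text should be corrected, and the correction is cheap.

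**What to change.** Put one DLT definition in 5.13 and have 5.2, 5.14 and 8.1 refer to it without restating it. The definition should:
- keep the safer rule of 8.1, so that a grade 2 intracranial haemorrhage within the DLT window is a DLT;
- use one attribution scope for every DLT: at least possibly related to the study drug or to protocol procedures, including infusion and catheter removal;
- keep the existing exceptions of 5.13, so that they apply to the primary endpoint as well.

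In 5.14, replace the grade 3 or 4 description of DLT by the reference to 5.13. The bleed can remain listed there as a reason to stop treatment.

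The cost is a few sentences in four sections, with no new assessment. There are two small downsides. Slightly more events will count as DLTs than under the present 5.13, and each grade 2 bleed will need an attribution judgement.
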